## Abstract

**Background:**

Subacromial impingement syndrome is the most frequent cause of shoulder problems which themselves affect 1 in 3 adults. Management commonly includes exercise and corticosteroid injection. However, the few existing trials of exercise or corticosteroid injection for subacromial impingement syndrome are mostly small, of poor quality, and focus only on short-term results. Exercise packages tend to be standardised rather than individualised and progressed. There has been much recent interest in improving outcome from corticosteroid injections by using musculoskeletal ultrasound to guide injections. However, there are no high-quality trials comparing ultrasound-guided and blind corticosteroid injection in subacromial impingement syndrome. This trial will investigate how to optimise the outcome of subacromial impingement syndrome from exercise (standardised advice and information leaflet versus physiotherapist-led exercise) and from subacromial corticosteroid injection (blind versus ultrasound-guided), and provide long-term follow-up data on clinical and cost-effectiveness.

**Methods/Design:**

The study design is a 2x2 factorial randomised controlled trial. 252 adults with subacromial impingement syndrome will be recruited from two musculoskeletal Clinical Assessment and Treatment Services at the primary-secondary care interface in Staffordshire, UK. Participants will be randomised on a 1:1:1:1 basis to one of four treatment groups: (1) ultrasound-guided subacromial corticosteroid injection and a physiotherapist-led exercise programme, (2) ultrasound-guided subacromial corticosteroid injection and an advice and exercise leaflet, (3) blind subacromial corticosteroid injection and a physiotherapist-led exercise programme, or (4) blind subacromial corticosteroid injection and an advice and exercise leaflet. The primary intention-to-treat analysis will be the mean differences in Shoulder Pain and Disability Index (SPADI) scores at 6 weeks for the comparison between injection interventions and at 6 months for the comparison between exercise interventions. Although independence of treatment effects is assumed, the magnitude of any interaction effect will be examined (but is not intended for the main analyses). Secondary outcomes will include comparison of long-term outcomes (12 months) and cost-effectiveness. A secondary per protocol analysis will also be performed.

**Discussion:**

This protocol paper presents detail of the rationale, design, methods and operational aspects of the SUPPORT trial.

**Trial registration:**

Current controlled trials ISRCTN42399123.

## Background

Painful shoulder problems are a common cause of impaired function and affect 1 in 3 adults [1,2], accounting for 1% of general practice (GP) consultations [3]. Subacromial impingement syndrome (SIS) is the most common cause of shoulder pain and affects approximately one-half of all shoulder pain sufferers [3]. SIS typically presents with pain during elevation of the arm, when a reduction in the space between the coracoacromial arch of the scapula and the humerus causes pinching of the subacromial/subdeltoid bursae, rotator cuff tendons and long head of biceps [4]. SIS is thought to arise as a result of bony abnormalities, rotator cuff weakness, impaired scapulohumeral rhythm, scapular instability and poor posture [4,5]. Treatment aims to reduce pain and increase function and UK management guidelines recommend exercise and corticosteroid injection in addition to patient education, oral analgesia and application of ice-packs [4,6]. In our recent observational study of patient outcome from treatment in primary-secondary care interface musculoskeletal clinics, 46% of patients with SIS received a corticosteroid injection and 38% were referred to a physiotherapist [7].

Exercise aims to reduce pain and functional impairment by improving posture, muscle strength, scapular stability and scapulohumeral rhythm [8]. It can be individualised, progressed and supervised by physiotherapists or self-guided from a leaflet containing standardised exercises [9]. Recent systematic reviews of exercise in SIS concluded that exercise decreases pain and improves function but that most trials are small, of poor quality, focus on short-term results only, and provide insufficient detail to allow firm conclusions to be drawn about the type, intensity, frequency and duration of exercise which is associated with best outcomes [10,11]. Consensus-based clinical guidelines recommend a ‘core’ set of exercises for SIS [4]. Studies in other musculoskeletal conditions support individualised, supervised and progressed exercise rather than a standard exercise approach [12] but, to date, there are few trials to guide exercise practice for patients with SIS [13-15].

Corticosteroid injections are commonly used to reduce pain and inflammation associated with SIS [16] although there is debate about their efficacy. Previous trials suggest similar effectiveness of corticosteroid injection and physiotherapy for both mixed shoulder problems [17,18] and SIS [19] whereas other trials report short-term superiority of injection over physiotherapy for mixed shoulder problems which is lost in the long-term [20,21]. A recent trial compared subacromial corticosteroid injection combined with exercise and manual therapy versus exercise and manual therapy alone for SIS and found similar improvements in pain and function at 3 months, however, more rapid reduction in pain and disability was seen in the group that received an injection [14]. These trials all used ‘blind’ shoulder injection, where the site of injection is located by observation and palpation. Poor response to blind injection has been attributed to misplaced injection [22-24].

Musculoskeletal ultrasound (MSUS) has become an increasingly accepted tool for guidance of therapeutic interventions [25,26]. However, although MSUS is low cost, can be carried out as a ‘bed-side’ procedure and has high resolution [26], few studies of ultrasound-guided (US-guided) injection for shoulder pain have been conducted. A recent RCT compared US-guided subacromial corticosteroid injection with systemic corticosteroid injection in patients with rotator cuff disease and found no difference in shoulder pain and function between groups at six weeks [27]. US-guided corticosteroid injection is suggested to provide greater improvements in pain, function and range of movement than blind injection for the treatment of SIS [28-30]. However, existing studies are small, of short duration, or are non-randomised, and none have originated from the UK [24,28-31].

The evidence supports the need for a high quality trial to determine how to optimise treatments for SIS patients and to reflect the complementary ways in which these interventions are used clinically i.e. that exercise and injection are often combined within the same package of care. The primary objectives of the SUPPORT trial (SUbacromial imPingement syndrome and Pain: a randomised controlled trial Of exeRcise and injecTion) are to assess whether (1) a physiotherapist-led intervention consisting of individualised, supervised and progressed exercise provides better improvements in pain and function than a standardised advice and exercise leaflet, and (2) US-guided subacromial corticosteroid injection provides better improvements in pain and function than unguided (blind) injection. Secondary objectives are to determine whether there is an interaction effect of combining US-guided injection and an individualised, supervised and progressed exercise programme and to conduct two separate cost-effectiveness analyses for the comparisons outlined in (1) and (2).

## Methods/Design

### Study design

The study will be a 2×2 factorial randomised controlled trial (Figure 1). Ethical approval has been obtained from The Black Country Research Ethics Committee (10/H1202/72).

**Figure 1 F1:**
[figure not shown]
Flow of participants through trial.

### Setting

Patients will be recruited through musculoskeletal interface clinics in Staffordshire and Stoke-on-Trent Partnership Trust. These services incorporate early referral to, and rapid assessment by, specialist clinicians (rheumatologists, rehabilitation medicine specialists, extended scope physiotherapists and general practitioners with a special interest (GPwSI)) within a multidisciplinary team-working environment. Local family practices will be informed about the trial.

### Participants

Consecutive patients referred from primary care to interface shoulder clinics will be assessed for eligibility by interface clinicians.

#### Inclusion criteria

•18 years and over

•No history of significant shoulder trauma, for example, fracture, clinically-suspected full thickness cuff tear

•A clinical diagnosis of SIS (pain in deltoid insertion area, positive Neer and Hawkins-Kennedy tests, pain on shoulder abduction).

Accurate diagnosis of SIS is challenging but combination of the patients’ history and response to Neer and Hawkins-Kennedy tests (to rule SIS out with a negative test) and pain on shoulder abduction (to rule SIS in with a positive test) provides optimal sensitivity and specificity [5]. Patients will not be required to undergo diagnostic imaging (eg MRI) to reflect current practice where treatment choices are informed by clinical findings.

#### Exclusion criteria

•Below 18 years old

•Those whose main complaint is due to neck problems, acromioclavicular pathology, or other primary shoulder disorders including adhesive capsulitis or clinically-suspected full thickness cuff tear

•Potentially serious pathology (inflammatory arthritis, polymyalgia rheumatica, malignancy etc) or ipsilateral shoulder surgery/replacement

•Those already on a surgical waiting list for shoulder surgery

•Contra-indications to local corticosteroid injection (known blood coagulation disorders, warfarin therapy)

•Participation in a shoulder-focused exercise programme or shoulder injection in the last month

•Inability to provide informed consent, complete written questionnaires, or read instruction leaflets written in English

### Initial contact with participants

All patients referred to musculoskeletal interface services at each site with shoulder pain, identified from the referral letter from primary care, will be triaged to an interface service shoulder clinic. One to two weeks prior to their appointment in the interface service shoulder clinic all patients will be sent a letter of invitation and a Participant Information Sheet (PIS).

### Interface service shoulder clinic

Patients will attend for their routine clinic appointment, according to normal NHS clinical attendance procedures. The interface clinician will undertake the clinical consultation according to usual practice. Patients who fulfil the criteria for a diagnosis of SIS will be asked by the interface clinician if they wish to be considered for trial participation. Patients who are interested in trial participation will be invited by the interface clinician to see a Research Nurse, who will further confirm eligibility and explain the trial in full. Ineligible patients and those who do not wish to participate in the trial will receive normal clinical care delivered by the interface clinician according to usual practice. Anonymised age and gender will be collected for those patients who decline to take part, in order to assess the external validity of the recruited sample of patients.

Eligible patients who are interested in the trial will be asked by the Research Nurse to provide written informed consent to participate. The Research Nurse will allocate the participant a unique study number. The participant will then complete a baseline questionnaire (Table 1). The Research Nurse will check the baseline questionnaire for completeness, before the participant is randomised.

**Table 1 T1:** Content of trial questionnaires

**Item**	**Baseline**	**6 weeks**	**6 months**	**12 months**
**Shoulder problem**				
Shoulder pain severity today (0-10 NRS)	X	X	X	X
Global change [20]		X	X	X
Potential adverse events		X		
Side of shoulder problem (right, left, both)	X			
Duration of shoulder problem	X			
History of previous shoulder problems	X			
Handedness (right or left)	X			
Shoulder Pain and Disability Index (SPADI) [32]	X	X	X	X
Effect of shoulder disability on typical everyday activities	X	X	X	X
Shoulder pain at night [33]	X	X	X	X
**Psychological factors**				
Brief illness perception questionnaire [34]	X	X	X	X
Pain self-efficacy questionnaire [35]	X	X	X	X
Tampa scale of kinesophobia [36]	X	X	X	X
**General health**				
EURO-QOL (EQ5D) [37]	X	X	X	X
MOS-Short Form 12 (SF-12) [38]	X	X	X	X
**Other health problems**				
Pain manikin	X	X	X	X
Co-morbidities	X			
**Treatment experiences, preferences, expectations**				
Previous experience of treatment	X			
Treatment preferences	X			
Expectations about different treatments	X			
Exercise adherence		X	X	X
**Confidence and satisfaction with treatment**				
Confidence in treatment		X	X	X
Treatment satisfaction		X	X	X
**Health-care utilisation**				
Consultation in primary and secondary care		X	X	X
Medication use (prescribed and over-the-counter)		X	X	X
Medical investigations		X	X	X
Hospital admission		X	X	X
**Effect of shoulder problem on work**				
Current/most recent job title and nature of work	X			
Current employment status	X	X	X	X
Work status including alteration in hours/duties	X			
Work absence	X	X	X	X
Work performance	X	X	X	X
Stanford presenteeism scale (SPS-6) [39]	X	X	X	X
Receipt of benefits, if not working	X	X	X	X
**Demographics**				
Age, gender	X	X	X	X
Living arrangements	X			
Height, weight	X			
Smoking status	X			

### Randomisation

As the Research Nurse will remain blinded to treatment allocation, a trial administrator in the interface service shoulder clinic will organise the randomisation, using Keele University’s Clinical Trial Unit’s telephone randomisation service, and then inform participants of their treatment allocation. Participants will be randomly allocated in a 1:1:1:1 ratio to 1 of 4 treatment groups using block randomisation to ensure that participants from each interface clinic have an equal chance of receiving any of the interventions:

•US-guided subacromial corticosteroid injection and physiotherapist-led individualised, supervised and progressed exercise

•US-guided subacromial corticosteroid injection and advice and exercise leaflet

•Unguided (blind) subacromial corticosteroid injection and physiotherapist-led individualised, supervised and progressed exercise

•Unguided (blind) subacromial corticosteroid injection and advice and exercise leaflet

The injection will be delivered in the same interface service shoulder clinic. Those randomised to receive the advice and exercise leaflet will receive this immediately following their injection. For participants randomised to receive the physiotherapist-led individualised, supervised and progressed exercise programme, the trial administrator will arrange their first physiotherapy appointment within 3 weeks of the shoulder injection, thereby meeting recommendations that recommendations that resistance exercise should be avoided for 2 weeks following steroid injection [4].

An evaluation of the success of Research Nurse blinding procedures will be completed and a procedure for reporting incidents where blinding has been compromised will be in place, through case report forms.

### Interventions

#### US-guided subacromial corticosteroid injection

Clinicians within the interface service shoulder clinics will deliver US-guided subacromial injection using a standard technique. Interface clinicians performing US-guided injections will comprise three rheumatologists, three extended scope physiotherapists, one musculoskeletal sonographer, one GPwSI, and one senior rheumatology nurse. Ultrasound examinations will be performed using the LOGIQe system with a 12 MHz transducer. The skin and transducer will be cleaned with chlorhexidine 0.5% solution and sterile gel will be applied to the transducer. The participant will be seated with the shoulder internally rotated and the ipsilateral hand placed on the buttock to allow greatest access to the subacromial bursa. The transducer will be placed anterolaterally and the hypoechoic subacromial bursa visualised. A 21G needle will be inserted under real-time US control until the needle-tip is seen to enter the bursa. A commercially available pre-mixed solution of methylprednisolone 40 mg and 1% lidocaine 1 ml will be injected in accordance with recent best-practice recommendations [4].

#### Unguided (blind) subacromial corticosteroid injection

Different interface clinicians to those providing the US-guided subacromial injections will deliver unguided (blind) subacromial injection using a standard technique. Unguided (blind) injectors will comprise two rheumatologists, one rehabilitation medicine specialist, four extended scope physiotherapists and a GPwSI. The participant will be seated with their arms hanging their by sides with elbow bent and forearm resting on lap. The skin will be cleaned with chlorhexidine solution 0.5%. A 21G needle will be inserted through the deltoid under the acromium process laterally and the same pre-mixed solution of methylprednisolone 40 mg and 1% lidocaine 1 ml will be injected.

Participants receiving either US-guided or unguided (blind) subacromial injection will be advised not to drive immediately after receiving the injection and to observe a period of relative rest for the following two weeks, avoiding pushing or pulling movements with the affected arm and heavy or repetitive tasks. Protocols for both US-guided and unguided injection will allow the injection to be repeated at the discretion of the treating interface clinician in event of partial response. In line with recommendations, a maximum of 2 injections will be permitted during follow-up per participant [4], and the number of injections received will be recorded.

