### Sample size

The trial is powered, at the 80% level, to detect a ‘small’ to ‘moderate’ effect size (standardised mean difference, 0.4) in shoulder pain and disability (SPADI) for the two main effects (US-guided injection versus blind injection; individualised, progressed and supervised exercise versus standardised advice and exercise leaflet). To address whether the physiotherapy-led intervention consisting of individualised, supervised and progressed exercise provides better improvements in pain and function than a standardised advice and exercise leaflet, we will use the total SPADI score at the 6 month time-point, as the primary outcome measure. Since previous trials have shown that corticosteroid injections improve pain and function more rapidly than exercise [14,20,21], we will use the total SPADI score at the 6 week time-point as the primary outcome measure for the comparison of US-guided and unguided (blind) injection.

A total sample size of 250 participants is needed given 80% power; 5% two-tailed significance; and assuming 20% loss to follow up.

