### Analysis

The primary intention-to-treat (ITT) analysis will be double-analysed independently by two blinded statisticians. Between-group analysis will be undertaken according to randomised allocation with retention of all participants throughout follow up for the purposes of full evaluation. The primary evaluations will be mean differences in total SPADI scores at 6 weeks between those randomised to receive US-guided injection versus unguided injection, and mean differences in total SPADI scores at 6 months between those randomised to physiotherapist-led individualised, supervised and progressed exercise versus advice and exercise leaflet. Secondary analyses will include comparison of pain and disability subscales of the SPADI; long-term SPADI outcomes (i.e. at 12 months); and analysis of other outcome measures. Estimates of clinical effect of the two main comparisons will be shown as percentage differences (for dichotomous outcomes) and mean differences (for numerical outcomes), with 95% confidence intervals. P-values will be given alongside statistical testing of the data. Multilevel longitudinal (mixed-) model regression methods (linear for numerical outcomes and logistic for dichotomous outcomes) will be used to generate estimates of effects. By including the baseline values as outcome the model retains all available data (as opposed to complete-case data only) and upholds the full intention-to-treat analytic criterion. An assumption of this approach is that the missing data is missing at random (MAR) – being dependent on baseline factors utilised in the model. Covariates included in the regression models are as follows: age, gender, baseline SPADI scores, duration of pain and location of clinic. Sensitivity analyses will include any other variables which are unbalanced between the groups at baseline.

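### Injectors are nested within injection arm (9 ultrasound-guided, 8 blind), but neither the stated model terms nor the sample size allow for differences between injectors

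*Protocol article*

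**What the plan says.** The two injection sections of the protocol article separate the clinicians by arm: "Different interface clinicians to those providing the US-guided subacromial injections will deliver unguided (blind) subacromial injection using a standard technique". The lists are explicit. For the guided arm: "Interface clinicians performing US-guided injections will comprise three rheumatologists, three extended scope physiotherapists, one musculoskeletal sonographer, one GPwSI, and one senior rheumatology nurse". For the blind arm: "Unguided (blind) injectors will comprise two rheumatologists, one rehabilitation medicine specialist, four extended scope physiotherapists and a GPwSI".

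The Analysis section names a multilevel longitudinal mixed model and ties it to retaining all available data when some are missing. It does not list the levels or random effects. It does fix the covariates: "Covariates included in the regression models are as follows: age, gender, baseline SPADI scores, duration of pain and location of clinic". Clinic is there; injector and physiotherapist are not.

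The Sample size section takes a target effect of "standardised mean difference, 0.4" for each main effect and concludes: "A total sample size of 250 participants is needed given 80% power; 5% two-tailed significance; and assuming 20% loss to follow up". It mentions no ICC or design effect.

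**The concern.** Patients treated by the same clinician may have more similar outcomes than patients treated by different clinicians. When no clinician works in both arms, that variation does not cancel out of the arm comparison. The difference between arms then contains the difference between two small sets of injectors. A model without an injector term treats that difference as if it came from about 200 independent patients.

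The protocol gives its own reason to expect some variation. The training section describes musculoskeletal ultrasound as strongly dependent on the operator. It also lets guided injectors qualify either through extensive experience or through an accredited course, followed by a competency test. The comparison at risk is one of the trial's two primary evaluations: total SPADI at 6 weeks.

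**Working it through.** **Inputs from the documents.** SMD 0.4 (so SD = 1), 80% power, 5% two-sided, 20% loss, total 250 (Sample size section). Allocation: "Participants will be randomly allocated in a 1:1:1:1 ratio to 1 of 4 treatment groups", so each injection margin is 1:1. Guided injectors: 3+3+1+1+1 = 9. Blind injectors: 2+1+4+1 = 8.

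**Assumptions (not in the documents).** Injector ICC of 0.01, 0.02 or 0.05; equal caseloads within arm; one injector per participant.

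**Step 1: reproduce the plan's figure.** Normal approximation: n = 2(1.96 + 0.842)²/0.4² = 98.1, so 99 per arm. The exact t-test needs 100 per arm, and 200/0.8 = 250, as stated. Power at 100 per arm is 80.7% (normal) or 80.4% (t). The figure therefore contains no allowance for clustering and almost no slack. The abstract's target, "252 adults with subacromial impingement syndrome will be recruited", gives 252 × 0.8 = 201.6 analysed, which changes nothing material.

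**Step 2: design effects.** Patients per injector: m = 100/9 = 11.1 (guided) and 100/8 = 12.5 (blind). The design effect (DE) in each arm is 1 + (m − 1) × ICC. At ICC 0.02 this is 1 + 10.1 × 0.02 = 1.202 and 1 + 11.5 × 0.02 = 1.230, mean 1.216.

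**Step 3: consequences.**
- Type I error if injector is ignored = 2(1 − Φ(1.96/√DE)), with the mean DE.
- Power (normal) = Φ(0.4/√((DE₁ + DE₂)/100) − 1.96).
- Power (t) uses the same standard error with 9 + 8 − 2 = 15 degrees of freedom.

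| Assumed ICC | Mean DE | Type I error, injector ignored | Power, normal | Power, t on 15 df |
|---|---|---|---|---|
| 0 | 1.00 | 5.0% | 80.7% | 75.3% |
| 0.01 | 1.11 | 6.3% | 76.6% | 71.0% |
| 0.02 | 1.22 | 7.5% | 72.7% | 66.9% |
| 0.05 | 1.54 | 11.4% | 62.5% | 56.8% |

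Simulating 40,000 trials per setting gave type I error of 5.0%, 6.3%, 7.4% and 11.2%. Coverage of the nominal 95% interval is about 93.7% at ICC 0.01 and 88.6% at 0.05. About five points of the power loss in the last column come from the 15 degrees of freedom alone, as the ICC 0 row shows.

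**Step 4: baseline adjustment.** The sample size takes no credit for it. Assume a baseline–outcome correlation of 0.5, so the residual variance is 1 − 0.25 = 0.75 of the raw variance, and let the ICC refer to the adjusted outcome.

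| Assumed ICC | Power, normal | Power, t on 15 df |
|---|---|---|
| 0 | 90.4% | 86.2% |
| 0.01 | 87.3% | 82.6% |
| 0.02 | 84.2% | 79.0% |
| 0.03 | 81.0% | 75.6% |
| 0.05 | 74.9% | 69.2% |

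Power of 80% survives to an ICC of about 0.03 by the normal approximation, but only to between 0.01 and 0.02 with t on 15 df. The type I formula depends on the DE, not on the residual variance, so baseline adjustment does not mend it.

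**The case against.** The best case against has four parts.

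- **The harm is conditional.** A reader might infer that the intervals are certainly too narrow. The documents do not support that: it needs an injector ICC above zero, and none is given. Standard techniques, the same pre-mixed solution in both arms, training, refresher sessions and audit should limit variation, and clinic may absorb some. This stands as a reason to word the point conditionally. It does not remove the point, because nothing shows that variation is eliminated, and a clinic term cannot capture differences among injectors within a clinic.
- **The model may already contain the term.** The levels of the mixed model are not listed, and an analysis plan that is not shown could add an injector level. That is fair, so it would be wrong to say that the trial will ignore injectors. But the article states a definite covariate list without a clinician, describes the model as longitudinal, and sizes the trial on independent patients. Those statements would still need reconciling with such a plan.
- **Power may be adequate.** A reader might infer that 80% power holds only if clinicians do not differ. That is true of the bare calculation, which has almost no slack, but not necessarily of the planned baseline-adjusted analysis (step 4).
- **One injector per participant is not established.** The protocol permits a second injection and does not say that the same clinician gives it. This stands, and the term should therefore be defined by the first injection.

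**Conclusion.** The point holds in conditional form. Full nesting of injectors in arm and the absence of any clustering allowance in the sample size follow directly from the text; the absence of an injector term is what the stated model implies. If injectors differ, the 6-week injection comparison is anticonservative: type I error is about 6.3% at an ICC of 0.01 and 11.4% at 0.05, given equal caseloads. Power on the plan's own inputs drops below 80% even at a small ICC. Whether it does so in the planned analysis depends on the ICC, the baseline correlation and the degrees of freedom, none of which the documents settle.

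Two limits apply. First, a random effect corrects precision only. It cannot separate ultrasound guidance from a systematic difference between the two clinician groups. The protocol discloses the separate groups, but its Discussion names only the lack of participant blinding as the main limitation. Second, a reader might extend these figures to physiotherapists. The documents do not allow it: physiotherapist clustering concerns the 6-month exercise comparison, arises in the physiotherapist-led arms only, and cannot be sized because the number of physiotherapists is not given.

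**What to change.** 1. In the Analysis section, add to the 6-week injection model a random intercept for the clinician who gave the first injection, nested in injection arm, with Satterthwaite or Kenward-Roger degrees of freedom. Where baseline SPADI is kept among the outcomes, let this effect act on post-injection visits only, since baseline is measured before randomisation.
2. For the 6-month exercise comparison, add a partially nested physiotherapist random effect, present in the physiotherapist-led arms only.
3. In the Sample size section, state that 80% power assumes zero clinician ICC, and show power over a range such as 0.01 to 0.05 with the matching degrees of freedom, with and without baseline adjustment.
4. State that the injection result compares guidance as delivered by two different groups of clinicians.

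Fix these before results are seen, since a later choice would be open to challenge.

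Cost: mainly wording, plus wider intervals and few degrees of freedom (about 15). Case report forms are completed by the clinicians, but the sponsor must confirm that clinician identity is captured for analysis. If the sponsor wanted to restore 80% power on the current inputs without crediting baseline adjustment, the total would be about 275, 313 or 554 at ICCs of 0.01, 0.02 and 0.05 (normal approximation, 17 injectors held fixed). With a baseline correlation of 0.5, the corresponding totals are about 200, 219 and 309, so 250 would be enough by that approximation at the two smaller ICCs.
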